### Assessment protocol

Each participant undergoes an entry visit (first study assessment) as soon as feasible after admission and informed consent. Follow-up assessments are scheduled within predefined poststroke windows at 5, 8, 12 and 24 weeks after stroke onset. As participants are eligible for inclusion within the first 8 weeks poststroke, they will complete between three and five assessments depending on their admission timing. Participants admitted later in the recovery trajectory (eg, around week 7–8 poststroke) will be scheduled at the first possible window and will subsequently be followed at the remaining scheduled windows (eg, weeks 8, 12 and 24) (figure 1).

All assessments are conducted by trained researchers, under standardised conditions in the hospital’s motion analysis lab (see further). Sessions are integrated into the rehabilitation schedule to minimise interference with therapy and last up to 120 min, including rest breaks as needed. When participants are discharged before a scheduled time point, outpatient follow-up is arranged whenever feasible.

The protocol consists of two components: (1) a series of structured, sensor-based recordings during functional activities obtained through an exergame and (2) a standardised set of clinical tests and PROMs, conducted without sensors. The clinical assessments and PROMs are completed whenever feasible, whereas the sensor-based exergame assessments are only performed when the participant is judged able to complete the respective task safely under supervision.

The sensor-based assessments are performed through an interactive game environment. The game interface (figure 1B) visualises an avatar, controlled by the participant’s non-paretic hand or a leg, who can move toward a target object. This game uses Kinect V2 markerless motion capture, placed in front of the participant, to track full-body movements in the frontal plane. Visual targets are presented on a screen to elicit controlled reaching or stepping movements. These tasks are designed to safely challenge postural control through controlled destabilisation and to elicit natural, functionally relevant movement responses.

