#### Statistical analysis

For the primary objective, longitudinal change in outcomes representing the four primary sensor-based domains (postural control, weight distribution, movement coordination and neuromuscular activity) will be analysed using linear mixed-effects models. Secondary longitudinal analyses will apply the same modelling framework to task-performance measures, daily activity, clinical outcomes and PROMs. Baseline characteristics will be summarised descriptively. Feasibility and data availability will be reported per assessment timepoint, documenting (1) the proportion of participants completing each assessment, (2) the number of valid trials per condition for sensor-based tasks and (3) reasons for missing data at each timepoint.

To investigate longitudinal change, each outcome will be modelled as a function of Time (categorical: baseline, week 5, week 8, week 12 and week 24). Models will include subject-specific random intercepts to account for baseline differences between individuals. Where supported by convergence and reliable variance estimation, random slopes for Time will be added to capture heterogeneity in individual recovery trajectories.^67
68^ Estimated marginal means will be used to describe group-level recovery trajectories, and post hoc contrasts will quantify differences across the full study period and between assessment intervals. Within each outcome domain, multiplicity will be controlled using Holm-Bonferroni correction.

Individual predicted trajectories will be visualised by combining individual intercept and slope estimates with the fixed effects. These individual trajectories will be plotted alongside group-level trajectories to illustrate both average trends and the distribution of recovery profiles across participants. Standard diagnostic checks will be performed; if assumptions are violated, transformations or alternative model specifications will be considered.

To examine associations between sensor-derived metrics of movement quality and clinical outcome measures, a multivariate mixed-effects modelling approach will be used. First, separate linear mixed-effects models will be fitted for each individual outcome, using the same model structure described above for the longitudinal analyses. These models provide subject-specific random intercepts and, when supported by convergence, random slopes for Time, representing each participant’s baseline level and rate of change.

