Next, bivariate (joint) mixed-effects models will be constructed to quantify the association between selected pairs of outcomes, that is, one sensor-derived metric and one clinical measure. Pairings will be defined based on theoretical considerations and clinical relevance. These models estimate the covariance between the random effects of the two outcomes, from which we will estimate (1) the correlation between random intercepts, reflecting the association between participants’ baseline sensor-based movement quality and their baseline clinical performance and (2) the correlation between random slopes, reflecting whether improvements in sensor-derived outcomes correspond to improvements on clinical measures over time.

Correlations will be interpreted descriptively using conventional thresholds (eg, negligible, low, moderate, high, very high). Because this aim is exploratory, α=0.05 will be used without correction for multiple comparisons. Associations will be visualised using scatterplots of individual random effects and bivariate trajectory plots.

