## Discussion

The FOSTER study is expected to provide longitudinal, multimodal data on postural control, movement quality, functional activity and PROMs during the first 6 months after stroke. By combining standardised clinical assessments with sensor-based measurements during functional tasks, the study may provide insight into aspects of recovery that are not fully captured by clinical scales alone, including changes in movement strategies and postural control during task performance. These data may help identify candidate sensor-derived markers of poststroke recovery and contribute rehabilitation-related data to the wider TARGET project.

Several practical challenges and limitations are anticipated. The single-centre, observational design may limit generalisability and preclude causal inference. Repeated multimodal assessments may also increase participant burden, particularly in people with fatigue, cognitive difficulties or more severe motor impairment. In addition, not all participants will be able to complete all sensor-based exergame tasks at each time point, especially early after stroke. Follow-up after discharge, particularly at 24 weeks, may be challenging because participants may need to return to the hospital.

To reduce these challenges, assessments are scheduled flexibly, rest breaks are provided when needed and sensor-based tasks are only performed when they are safe and feasible. After discharge, participants are asked whether they are willing and able to continue follow-up and participation remains entirely voluntary. When participants continue outpatient rehabilitation at the hospital, follow-up assessments are aligned with their scheduled appointments whenever possible. Travel costs are not reimbursed, which may contribute to loss to follow-up after discharge.

By contributing longitudinal, multimodal rehabilitation data across stroke aetiologies, FOSTER will complement TARGET’s broader development of health virtual twin models for AF-related stroke. Although the FOSTER cohort is not restricted to AF-related stroke, these data may help inform future data-driven models of poststroke recovery and personalised rehabilitation.

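### The spread of predicted individual trajectories is offered as the distribution of recovery profiles, but predicted effects are shrunken, so heterogeneity in rate of change will look too small

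*Protocol article*

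**What the plan says.** The Statistical analysis section fixes how the individual curves are built: "Individual predicted trajectories will be visualised by combining individual intercept and slope estimates with the fixed effects". It also fixes their use. They are plotted next to the group trajectory "to illustrate both average trends and the distribution of recovery profiles across participants". The random part of the model is conditional: "Where supported by convergence and reliable variance estimation, random slopes for Time will be added to capture heterogeneity in individual recovery trajectories". Otherwise only random intercepts remain. The fixed part treats Time as categorical with five levels, and the form of the random slope is left open.

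For the sensor-clinical associations, the same section takes the correlations from bivariate mixed models and adds: "Associations will be visualised using scatterplots of individual random effects and bivariate trajectory plots".

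On data per person, the Assessment protocol section says that participants are planned so that "they will complete between three and five assessments depending on their admission timing". Two other places point to fewer in practice. The Outcome measures section lets exergame recordings start only once the tasks are safe for the participant. The Discussion says: "Follow-up after discharge, particularly at 24 weeks, may be challenging because participants may need to return to the hospital". It adds that unreimbursed travel may contribute to loss. No dropout rate and no variance figures are given.

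**The concern.** A predicted random effect is a compromise between a person's own data and the group mean. The less a person's data say about slope, the closer the prediction lies to what the group (and that person's level) would suggest. The spread of predicted slopes is therefore not an estimate of the between-person spread of slopes. It is smaller by construction, and the gap depends on how many visits each person has and how they are spaced.

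The plan gives this spread the task of showing how recovery profiles are distributed. Heterogeneous recovery that is hard to predict for the individual is the study's stated rationale, and the data are meant to feed individualised models. A figure that makes rates of recovery look more uniform than the fitted model itself says they are would misdescribe a central descriptive result. The primary outcome domains are the sensor-based ones, where short individual series are most likely.

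**Working it through.** The plan has no figure of its own to reproduce here. The target of 100 participants is pragmatic and plays no part in the point.

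**Inputs.** From the article: scheduled weeks 5, 8, 12 and 24, an entry visit, and three to five visits per person. Assumed, because the article gives none of them: entry at week 4, random-intercept SD 1, SD of individual change over 20 weeks 0.7, residual SD 0.5, intercept-slope correlation -0.2, and a linear random slope with time t = (week - 4)/20.

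**Formula.** With G the random-effect covariance matrix, Z the person's design matrix and V = ZGZ' + σ²I, the predicted effects have covariance GZ'V⁻¹ZG. The square root of its slope entry divided by the slope entry of G is the ratio of the SD of predicted slopes to the true slope SD.

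**One visit, by hand.**
- At week 4 (t = 0) the ratio is |ρ|/√(1 + σ²) = 0.2/√1.25 = 0.18.
- At week 8 (t = 0.2) the covariance of slope and observation is -0.14 + 0.49 × 0.2 = -0.042. The variance of the observation is 1 - 0.056 + 0.0196 + 0.25 = 1.2136. The ratio is 0.042/(0.7 × √1.2136) = 0.05.

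**All visit patterns (residual SD 0.5).**

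| Visits (weeks) | Correlation -0.2 | -0.5 | +0.5 |
|---|---|---|---|
| 4, 5, 8, 12, 24 | 0.75 | 0.76 | 0.81 |
| 8, 12, 24 | 0.64 | 0.64 | 0.78 |
| 4, 5 | 0.18 | 0.46 | 0.49 |
| 8, 12 | 0.19 | 0.35 | 0.62 |
| 4 only | 0.18 | 0.45 | 0.45 |
| 8 only | 0.05 | 0.34 | 0.54 |

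With residual SD 0.3 or 0.7 (correlation -0.2), the five-visit ratio is 0.88 or 0.63.

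**Level.** At correlation -0.2 and residual SD 0.5, the predicted week-24 level keeps 0.70 to 0.85 of its true SD in the one- and two-visit patterns tabulated. Level is shrunk far less than change.

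**The whole plot.** Suppose a share d is lost, half after week 4 and half after weeks 4 and 5, and the rest have five visits. The SD ratio for all plotted slopes is √[(1 - d) × 0.75² + d × 0.18²], computed with unrounded ratios (0.751 and 0.179). This gives 0.75 with no loss, 0.68 at d = 20% and 0.59 at d = 40%.

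**What the fitted model itself says.** This was simulated with 100 participants, categorical fixed Time, a random intercept and a linear random slope, fitted by REML, 25 runs per setting. With SD of change 1.0, residual SD 0.5 and correlation 0, the plotted slopes had 0.86, 0.76 and 0.62 of the true SD at 0, 20 and 40% loss. The model's estimated slope SD was 1.01, 0.99 and 0.95 of the truth. Over all three settings simulated, the estimated SD stayed within 0.95 to 1.06.

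**No random slope.** If the convergence rule removes the slope, each curve is the group curve plus a constant. The plotted spread of change is exactly zero, whatever the truth.

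**The case against.** The strongest reply is that this concerns a figure. The plan says the plot illustrates, it computes no SD or test from the predicted effects, and it estimates heterogeneity through the random slopes. That stands, and it limits the point: no estimate or inference changes. Completion and reasons for missing data will also be reported per time point, so readers will see the attrition. That report does not tell them how far the plotted spread has been compressed.

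Several stronger readings are tempting, and the document does not support them.

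- A reader might infer that participants lost early are drawn out to week 24 as if observed. The article does not say how far any line runs, and line extent is a detail that an article may leave to a fuller document.
- A reader might infer that such participants are shown as average recoverers. Only their rate of change is drawn toward the average. Most of their level is kept, so their lines run roughly parallel to the mean, not on it. With a strong intercept-slope correlation, even the slopes keep about a third to three fifths of their spread.
- A reader might blame dropout alone. Five-visit participants are already at about 75% in the assumed case.
- A reader might think the reported sensor-clinical correlations are distorted. The plan takes them from the joint models, and only the accompanying scatterplots carry the shrinkage.

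It is also fair that every size above is assumed, and that the calculation uses a linear random slope whose form the article leaves open.

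**Conclusion.** The point holds in a limited form. The article states both a construction and a use, and the construction does not serve the use: predicted trajectories understate the between-person spread in rate of change, for completers as well as for participants with few visits. In the assumed case the plotted slope SD is about 75% of the truth with five visits, 64% with weeks 8, 12 and 24, 18-19% with two visits (weeks 4 and 5, or 8 and 12) and 5-18% with one. With a correlation of ±0.5 the one- and two-visit figures are about 34-62%. If random slopes are dropped, the plot shows no heterogeneity of change at all.

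The direction follows from the method. The size rests on variances, a correlation and a dropout share that the document does not give. Fixed effects are unaffected, and so are the variance components and joint-model correlations, provided that missingness depends only on observed data. This is a modest matter of description that should be corrected before analysis.

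**What to change.** Change the stated source of the distribution of recovery profiles. Report the estimated random-effect SDs with confidence intervals, or a 10th-90th percentile band around the mean trajectory built from the estimated variances. Where the random slope was dropped, say so, and do not read the parallel lines as evidence of uniform recovery.

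Keep the individual predicted curves as illustration only. Label them as shrunken predictions, draw them over the observed points, and dash any part beyond a participant's observed visits. In the random-effect scatterplots, mark the number of visits behind each point. No minimum number of visits need be imposed, since nothing in the document supports a particular cutoff.

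The cost is a little more analysis and plotting work, with no new data. Recruitment and follow-up are still under way, so it can be settled before analysis. One limitation should be stated with it: the percentile band relies on normally distributed random effects.

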## Ethics and dissemination

The study is conducted in accordance with the Declaration of Helsinki and the General Data Protection Regulation (EU 2016/679). Ethical approval was granted by the Ethics Committee of Rehabilitation Hospital Inkendaal (B.U.N. 2024-TEE-002). The study is registered at ClinicalTrials.gov (NCT06806761). Potential participants receive oral and written information about the study’s objectives and procedures before providing written informed consent; where decision-making capacity is lacking due to language or cognitive impairment, consent will be obtained from a legally authorised representative in line with Belgian legislation. Participants who later regain capacity will be re-consented (within the ≤8-week window).

Assessments involve low-risk functional tasks under direct supervision by a licensed physiotherapist; participants may pause or stop at any time. Predefined stopping criteria apply (eg, fatigue/instability, near-fall, dizziness, chest pain or clinician concern). Adverse events are recorded; serious events are reported per institutional policy.

Results will be presented at national and international scientific meetings and submitted to peer-reviewed journals; institutional websites and media offices may also be used. Pseudonymised data and metadata will be deposited in a secure institutional repository and on the TARGET data platform after study completion under controlled access and curated according to the study’s data management plan; external requests will be considered via the corresponding author under a data-use agreement.

## Discussion

The FOSTER study is expected to provide longitudinal, multimodal data on postural control, movement quality, functional activity and PROMs during the first 6 months after stroke. By combining standardised clinical assessments with sensor-based measurements during functional tasks, the study may provide insight into aspects of recovery that are not fully captured by clinical scales alone, including changes in movement strategies and postural control during task performance. These data may help identify candidate sensor-derived markers of poststroke recovery and contribute rehabilitation-related data to the wider TARGET project.

Several practical challenges and limitations are anticipated. The single-centre, observational design may limit generalisability and preclude causal inference. Repeated multimodal assessments may also increase participant burden, particularly in people with fatigue, cognitive difficulties or more severe motor impairment. In addition, not all participants will be able to complete all sensor-based exergame tasks at each time point, especially early after stroke. Follow-up after discharge, particularly at 24 weeks, may be challenging because participants may need to return to the hospital.

To reduce these challenges, assessments are scheduled flexibly, rest breaks are provided when needed and sensor-based tasks are only performed when they are safe and feasible. After discharge, participants are asked whether they are willing and able to continue follow-up and participation remains entirely voluntary. When participants continue outpatient rehabilitation at the hospital, follow-up assessments are aligned with their scheduled appointments whenever possible. Travel costs are not reimbursed, which may contribute to loss to follow-up after discharge.

By contributing longitudinal, multimodal rehabilitation data across stroke aetiologies, FOSTER will complement TARGET’s broader development of health virtual twin models for AF-related stroke. Although the FOSTER cohort is not restricted to AF-related stroke, these data may help inform future data-driven models of poststroke recovery and personalised rehabilitation.
